# A peer-volunteer led active ageing programme to prevent decline in physical function in older people at risk of mobility disability (Active, Connected, Engaged [ACE]): study protocol for a randomised controlled trial

**DOI:** 10.1186/s13063-023-07758-3

**Published:** 2023-11-29

**Keywords:** Physical activity, Disability prevention, Well-being, Peer-volunteers, Frailty, Mobility, Community, Randomised controlled trial

## Abstract

**Background:**

The Active Connected Engaged [ACE] study is a multi-centre, pragmatic, two-arm, parallel-group randomised controlled trial [RCT] with an internal pilot phase. The ACE study incorporates a multi-level mixed methods process evaluation including a systems mapping approach and an economic evaluation. ACE aims to test the effectiveness and cost-effectiveness of a peer-volunteer led active ageing intervention designed to support older adults at risk of mobility disability to become more physically and socially active within their communities and to reduce or reverse, the progression of functional limitations associated with ageing.

**Methods/design:**

Community-dwelling, older adults aged 65 years and older (*n* = 515), at risk of mobility disability due to reduced lower limb physical functioning (Short Physical Performance Battery (SPPB) score of 4–9 inclusive) will be recruited. Participants will be randomised to receive either a minimal control intervention or ACE, a 6-month programme underpinned by behaviour change theory, whereby peer volunteers are paired with participants and offer them individually tailored support to engage them in local physical and social activities to improve lower limb mobility and increase their physical activity. Outcome data will be collected at baseline, 6, 12 and 18 months. The primary outcome analysis (difference in SPPB score at 18 months) will be undertaken blinded to group allocation. Primary comparative analyses will be on an intention-to-treat (ITT) basis with due emphasis placed on confidence intervals.

**Discussion:**

ACE is the largest, pragmatic, community-based randomised controlled trial in the UK to target this high-risk segment of the older population by mobilising community resources (peer volunteers). A programme that can successfully engage this population in sufficient activity to improve strength, coordination, balance and social connections would have a major impact on sustaining health and independence.

ACE is also the first study of its kind to conduct a full economic and comprehensive process evaluation of this type of community-based intervention. If effective and cost-effective, the ACE intervention has strong potential to be implemented widely in the UK and elsewhere.

**Trial registration:**

ISRCTN, ISRCTN17660493. Registered on 30 September 2021.

Trial Sponsor: University of Birmingham, Contact: [name], Head of Research Governance and Integrity; Email: [contact].

Protocol Version 5 22/07/22.

**Supplementary Information:**

The online version contains supplementary material available at 10.1186/s13063-023-07758-3.

## Background

During old age, people gradually transition from independence and adequate physical function to frailty and mobility disability [1, 2]. Mobility disability, defined as a reduced ability to walk or balance, increases rapidly with age and generates major societal challenges. These include costs for people with mobility limitations such as loss of independence, risk of falls and reduced quality of life; costs to friends/family who provide care, and increased health and social care costs [3, 4]. Among adults aged over 70, 38% are classed as frail or pre-frail (defined as scoring 9 or less on the Short Physical Performance Battery (SPPB)) [1, 5]. Frail or pre-frail older people have a substantially higher risk of major mobility disability (OR = 8.3 (95% CI: 3.3 to 20.7) [5] and mortality (HR 2.6 to 5.3) [6] compared with non-frail older adults.

Increasing physical activity can prevent or delay progression of frailty and mobility disability [7, 8]. However, there is a clear trend of declining physical activity over time in people aged over 65 [9]. Reasons for this include the lack of a companion to go out with, low confidence to engage with community initiatives, and perceived safety of engaging with activity [10]. A recent systematic review of reviews examined interventions that were efficacious or effective in increasing uptake of physical activity in older people (17 studies; *N* = 79,650) and reported barriers to and facilitators of active ageing (9 studies; *N* = 22,413). Access to role models, peer and community support, individual tailoring of interventions, making exercise enjoyable and sociable, and feelings of ownership of interventions were identified as key enablers of physical activity [11].

A 2019 National Institute of Health Research (NIHR) review of UK-based physical activity interventions for older people [12] identified only two volunteering programmes, a peer-led walking group feasibility trial [13] and our Active Connected Engaged [ACE] feasibility trial [14]. This review highlighted the need for more robust evidence for such approaches ensuring that they incorporate theories of behaviour change; focus on social enablers of exercise; and target people with poor lower limb strength and/or weaker social networks.

Interventions that can successfully increase levels of physical activity and enhance social connections, leading to the delay or prevention of functional decline would have substantial public health value.

## Methods

### Trial design

The study protocol is presented in accordance with the Standard Protocol Items: Recommendations for Interventional Trials (SPIRIT) guidelines (Additional file 1).

The ACE study is an individually randomised, parallel-group, single-blind RCT with an internal pilot phase, a multi-level (individual and systems level), mixed-methods process evaluation and an economic evaluation. Following identification and recruitment, 515 patients who meet the study inclusion criteria will be randomised to receive either the ACE intervention, delivered over a period of 6 months by peer volunteers, or a minimal control intervention. Participants will be individually randomised to the intervention and control arms in a 1:1 ratio, stratified by site, using a centralised web-based system run by the Cardiff Centre for Trials Research.

The primary objective of the ACE study is to assess the effectiveness of a peer-volunteer led active ageing intervention for reducing the progression of mobility-related functional limitations in older people, who are at high risk of transition from independence to mobility-related disability. Secondary objectives are to compare participants allocated to the ACE programme with the control group in terms of levels of physical activity, psychological functioning and well-being, health-related quality of life, capability, activities of daily living, cognition, social networks and reduced sedentary time, loneliness, pain, falls, fear of falling and utilisation of health and social care.

The internal pilot phase will assess the feasibility of recruitment methods (allowing for some refinement if needed) and confirm adequate participant retention rates in the study, prior to progressing with the main trial (Additional file 2). Primary and secondary outcome data will be collected at baseline, 6, and 18 months. Selected secondary outcomes will also be assessed at 12 months.

The ACE study will be conducted at four UK sites (West Midlands, Greater Manchester, South Wales and Bristol), allowing recruitment of a socio-economically and ethnically diverse sample. At the delivery site in Wales, the study will be known as ACTIF, with the qualifier ‘known in England as ACE’ on documentation. This is to avoid any confusion with the ACE (Adverse Childhood Experiences) programme in Wales [15].

### Study population

The eligibility criteria are intended to identify sedentary, community-dwelling, older people aged 65 and over with lower limb functional limitations (i.e. at risk of major mobility limitations) but who are still ambulatory, i.e. they can still walk. This will be measured using a battery of objective physical function tests (SPPB) to assess balance, walking speed and the ability to move from a sitting to a standing position. This generates a physical function score from 0 to 12. Older adults with scores of 4–9 (inclusive) out of 12 will be eligible to take part in ACE. This is based on data showing that older adults with SPPB scores of 9 or less have a substantially higher risk of major mobility disability 3 years later (OR = 8.3 (95% CI: 3.3 to 20.67) compared with those with a score of 12 [5, 8]. Inclusion and exclusion criteria for participants and peer volunteers are summarised in Table 1.

**Table 1 Tab1:** Inclusion and exclusion criteria for the selection of participants and peer volunteers

	**Participants**
**Inclusion criteria**	• Adults aged 65 or older who are not in full-time employment • Being at risk of major mobility disability (score between 4 and 9 (inclusive) on the Short Physical Performance Battery (SPPB)^a^ • Planning to reside in the target area (West Midlands, Greater Manchester, South Wales or Bristol) for at least 18 months
**Exclusion criteria**	• Self-reported high level of mobility^b^ or SPPB score above 9 at baseline screening • Self-reported inability to walk across a room without a walking aid other than a walking stick, or using a wheelchair or Zimmer frame • Existing major mobility limitation (defined as SPPB of 3 or less, or unable to complete the 4-m walk component of SPPB) • Living in residential or nursing care • Inability to meet regularly with an ACE volunteer • A documented or patient-reported medical condition that would preclude participation, including: o Severe arthritis that prevents participation in physical activity; o Parkinson’s disease or diagnosed dementia o Any terminal illness o Lung disease requiring use of orally administered corticosteroids or supplemental oxygen o Severe kidney disease requiring dialysis o Severe heart disease or an implanted cardiac defibrillator o Cardiac arrest which required resuscitation o Receiving radiation therapy or chemotherapy treatment for cancer o Awaiting knee or hip surgery o Major heart surgery in the last 6 months o Unstable heart condition (e.g. uncontrolled arrhythmia, angina, heart failure or hypertension) o Spinal surgery in the last 6 months o Any other clinical condition that the person’s GP or clinician considers would make them unsuitable for participation in an exercise programme
**Temporary exclusion criteria**	• Heart attack (or myocardial infarction), stroke, spinal surgery, hip fracture, hip or knee replacement within the previous 6 months • Currently receiving physical therapy on legs or enrolled in another physical activity research or intervention study
	**Peer volunteers**
**Inclusion criteria**	• Community-dwelling • Aged 55 years and older • SPPB scores of 4 and above • Not in full-time employment (unless with flexibility to volunteer during weekdays)
**Exclusion criteria**	• Not available to volunteer in the daytime during the week

^a^ Based on definitions of physical frailty from the European Medicines Agency, this guidance defines pre-frailty as an SPPB score of 8–9 and frailty as an SPPB score of 7 or less. ^b^ At screening reported that all of the following tasks are ‘easy to perform’: walking across a room, getting out of a low chair, walking up a flight of stairs with no handrail or wall to lean on and walking on uneven pavement without losing balance

### Recruitment

A range of recruitment strategies to identify suitable participants and peer-volunteers will be employed:

#### Primary care

General practitioner (GP) practices in the study catchment areas will be invited to participate through their local Clinical Research Network (CRN) and other networks. Where possible we will select practices to maximise diversity in terms of ethnicity and socio-economic status.

Practice staff will search the practices’ electronic patient databases for potentially eligible patients using the trial entry criteria (for criteria that are coded in the database). Lists generated from the searches will be reviewed by a GP to screen for items that are not included in the electronic searches. A Patient Approach Letter (PAL) printed on the practice headed notepaper, a reply form, Participant Information Sheet (PIS), and one-page study summary will be sent to suitable patients, with a pre-paid reply envelope addressed to the research team at the local trial site. The reply form will allow people to indicate whether they are interested in being a study participant or a peer-volunteer. GPs and practice nurses may also offer the recruitment pack in surgery to suitable patients.

#### Third sector organisations

The Principal Investigators at each trial site will engage with Voluntary, Community or Social Enterprise (VCSE) organisations and authorities working with adults over the age of 65 to identify potentially eligible service users. Publicity materials will be made available through libraries, supermarkets, post offices and GP surgeries.

#### Word-of-mouth and snowball sampling

To enhance recruitment, we will use word-of-mouth and snowball sampling techniques and employ the assistance of bi-lingual community champions.

#### Local media

Recruitment will be supported by a low-cost public relations campaign targeting local radio and community events.

Each ACE trial site will track recruitment methods to determine the most successful strategy particularly for recruiting from diverse ethnic groups.

### Eligibility screening

The eligibility of respondents will be assessed in a two-step sequential screening process:*Phone-based screening:* After gaining verbal consent a preliminary phone screen will check inclusion and exclusion criteria that can be assessed by phone (e.g. self-reported inability to walk across a room), including a second check on medical exclusion criteria (e.g. recent heart surgery). Ability to attend intervention sessions will also be checked. Potential peer-volunteers will be contacted by telephone to check inclusion and exclusion criteria (age >  = 55 years, not in full-time employment unless working flexibly), and to collect their demographic data (Additional file 5).*Face-to-face screening sessions:* Potentially eligible participants and peer-volunteers will then be invited to a group-based assessment session. The SPPB gait speed test will be conducted first, and those who fail to complete the 4-m walk or do not meet the other SPPB inclusion criteria will be thanked for their time and signposted to other suitable activities/services.

### Consent

Older adults who are willing to take part in ACE will be asked to provide written informed consent to the local research team prior to commencement of the face-to-face screening sessions (Additional file 6).

### Randomisation/allocation

Eligible participants will be randomised to one of the two arms in a 1:1 ratio stratified by site (West Midlands, Greater Manchester, South Wales and Bristol), using a centralised web-based system run by the Cardiff University Centre for Trials Research (CTR).

To perform randomisation an authorised member of the research team will access the randomisation website using unique username and password log-in details. The website will require entry of patient’s initials, date of birth and stratification variable. The randomisation website will also generate a unique study ID number for the participants when they are randomised. In the relatively unlikely event that two people from the same household present for screening, to avoid the potential for contamination (if they were allocated to different groups), only the first would be included in the study. This, and the reasoning behind it, will be carefully explained during the telephone screening process.

### Implementing the allocation sequence

The local site Research Associate will telephone participants to inform them of their allocation and will send a confirmation letter. The local site Research Associate will therefore not be blinded to allocation. Main outcome assessors at 6 and 18 months will be blinded.

To maximise retention, we will offer a voucher-based incentive for completion of assessments at 6 and 18 months. The control group will also be invited to two social events with a presentation on healthy ageing to encourage continuing engagement in the trial. Newsletters will also be distributed to all participants at the end of each project year.

### Intervention

Participants in the intervention arm will receive a 6-month active ageing programme, using peer volunteers to deliver individually tailored, and person-centred support to help inactive, less mobile older people to ‘get out and about’ to engage with their local community, with the aim of increasing physical activity. This is intended to lead to improvements in their mobility (specifically lower limb physical functioning) [14], as well as improvements in their physical and mental well-being and social connectedness.Peer volunteers will meet participants twice in one-to-one meetings supporting them to identify local activities of interest and address barriers to participation (motivation stage: first 2 weeks). The particular relevance/benefits of activities that might improve lower limb physical function (i.e. those including a significant strength and balance component) will be discussed.The volunteer-participant pair will attend at least three local initiatives chosen by the participant (action stage: month 1–3). We are collaborating with exercise providers for older adults in all three sites to ensure participants have opportunities to attend activities that specifically target lower limb physical function.Telephone support to continue attending local activities. At least two further joint visits will be scheduled as support “tails off” (maintenance stage: months 3–6).

#### Control arm

After completion of baseline assessments, participants allocated to the control group will be invited to two, 60–90-min group sessions over the 18 months of the study. The sessions will be scheduled close to the 6- and 18-month assessment points and will consist of presentations and discussions on various aspects of healthy ageing (excluding physical activity).

### Underpinning theory

ACE draws on the Process Model of Lifestyle Behaviour Change (PMLBC) and Self Determination Theory [16, 17]. These two overlapping and mutually compatible theoretical frameworks provide the main principles and processes for supporting behaviour change in the ACE intervention. The ACE logic model illustrates how the intervention is theorised to lead to changes in short and longer-term outcomes, and how contextual (including system-level) processes might influence its operation (Additional file 3). These factors are consistent with qualitative feedback obtained from volunteers in the ACE feasibility study [14].

The ACE volunteer training is designed to teach volunteers how to use person-centred communication skills to build and sustain the motivation and engagement of the volunteers, through self-efficacy, positive feedback and fulfilment of the volunteer’s needs and expectations. It also includes teaching volunteers to guide participants along an individually tailored “road map” for behaviour change, based on three key stages: getting motivated; making a plan; and supporting behaviour maintenance.

Peer volunteers will attend a one-day training course delivered by ACE researchers. The course was developed and tested in the ACE feasibility study [14], and further refined in the ACE internal pilot in consultation with the Royal Voluntary Service. It will include (i) skills for developing and reinforcing motivation (person-centred counselling for supporting fundamental (SDT-related needs); (ii) how to identify local activity options and develop individually tailored plans based on participants’ needs /preferences; (iii) the need to build lower limb function (strength and balance) and types of exercise /activity associated with this; (iv) solution-focused methods for avoiding /overcoming barriers; and (v) maintenance support techniques. The training programme emphasises that the ACE volunteer’s role is to support the individual in becoming autonomous and responsible for making decisions about physical activity and social engagement within their local communities.

ACE volunteers will be managed and supported by local volunteer management partners such as RVS and AGE UK Bristol. NHS/government COVID-19 guidelines will be adhered to throughout all phases of the ACE intervention.

#### Steps to ensure intervention fidelity

We will enact strategies suggested by the NIH Behaviour Change Consortium to support intervention fidelity [18]. We will ensure “design fidelity” and “training fidelity” by building our intervention and training course around a clear logic model (Additional file 3). To support “delivery fidelity” we will encourage regular meetings between volunteers in order to (i) share their experiences and best practice, (ii) refresh principles covered at training and (iii) address any queries they have. To support “receipt” and “enactment” (understanding and use of behaviour change strategies by participants), we will encourage individual tailoring of intervention delivery by the facilitators, and reviewing of progress (including use of self-monitoring, sustainability-focused action-planning and problem-solving).

### Measures

A full list of measures and time-points are presented in Table 2. A copy of the Participant Case Report Form is included in Additional file 7. All questionnaires will be checked for completeness prior to participants leaving the assessment. Any missed questions will be brought to the attention of the participant for completion.

**Table 2 Tab2:**
[figure not shown]
ACE screening and assessments for participants (P) and peer volunteers (V)

^1^Telephone screening, ^2^Face-to-face screening and baseline assessment, ^3^6-month follow-up, ^4^12-month follow-up, ^5^18-month follow-up

### Sample size calculation

The ACE trial will recruit a total of 515 participants across four study sites.

Effect Size: The primary aim is to assess the long-term (18-month) effect of a peer volunteering/physical activity intervention on changes in SPPB scores. A difference of 0.5 points in the SPPB score has been defined as a minimum clinically meaningful change [8, 19].

Using baseline data from 777 adults with the same inclusion criteria as we propose for this study (from our REACT trial [20, 21]), the standard deviation for SPPB scores in this population is 1.56. This is identical to the standard deviation observed for SPPB scores in the US-based LIFE trial (SD = 1.6, *N* = 1635). To detect a difference of 0.5 points in SPPB with 90% power and 5% significance, 206 participants are required per arm. Assuming a 20% loss to follow-up at 18 months [based on a 19% loss to follow-up at 24 months in our REACT study], the total sample size required is 515.

We will recruit a minimum of 130 volunteers (aged 55 + years) to support two intervention participants each. Since the cluster sizes in the intervention arm are minimal (less than two participants to each volunteer on average) we will not inflate the sample size required for clustering at the level of volunteer. However, the analytic strategy will present results from a partial cluster model to assess the small amount of possible clustering in the intervention arm only.

### Statistical analysis

Primary outcome analysis will be undertaken blinded to group allocation and will be on an intention-to-treat (ITT) basis with due emphasis placed on confidence intervals. Using appropriate descriptive statistics we will assess any imbalance between the trial arms at baseline and describe the characteristics of participants. The primary analytic strategy will employ a linear mixed model including baseline, 6- and 18-month SPPB outcome time points as well as the randomisation stratification variable (site). Treatment and time variables together with a categorical treatment by time interaction will be fitted to explore treatment effects over time. All results will be presented with 95% confidence intervals and *p*-values. A partial cluster regression model to account for the possible clustering effects of participants within volunteers will also be fitted to the primary outcome within the mixed model framework. Intra-cluster coefficients will be estimated and reported if non-negligible.

Depending on the extent of missing primary outcome data, the primary analysis will be repeated using the complete data set generated using multiple imputations. Sensitivity analyses will be conducted to investigate the potential effects of non-random missing data and of any co-interventions on the results and conclusions.

Secondary outcome analysis will be undertaken using the same general approach as for the primary analysis, using the baseline, 6-, 12- and 18-month follow-up data. This will include linear or generalised linear mixed regression models for continuous or binary outcomes as appropriate.

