#### Adjusted analysis

While we are not expecting a significant imbalance between groups, variables such as age and biological sex may be considered for inclusion in the primary model.

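### The primary model treats baseline SPPB as an outcome with a free arm difference, so either available 18-month contrast is less precise than a baseline-adjusted one that would cost nothing

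*Protocol article*

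**What the plan says.** The Statistical analysis section specifies a "linear mixed model including baseline, 6- and 18-month SPPB outcome time points", with site as the stratification variable. It continues: "Treatment and time variables together with a categorical treatment by time interaction will be fitted to explore treatment effects over time". It does not say that the arms share a baseline mean, and it does not list baseline SPPB as a covariate. The Adjusted analysis section adds only that "variables such as age and biological sex may be considered for inclusion in the primary model".

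The 18-month effect is described in two ways. The abstract has "The primary outcome analysis (difference in SPPB score at 18 months", which is a comparison of levels. The Sample size calculation section states the primary aim as the long-term "effect of a peer volunteering/physical activity intervention on changes in SPPB scores". The Statistical analysis section does not say which coefficient or combination carries the primary result.

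The sample size rests on a cross-sectional SD and has no correlation term: "the standard deviation for SPPB scores in this population is 1.56", and "To detect a difference of 0.5 points in SPPB with 90% power and 5% significance, 206 participants are required per arm".

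**The concern.** Write the mean at visit t as μ_t + arm × (β + γ_t), with γ = 0 at baseline. As described, β is a free parameter: the arm difference at baseline. The model then offers two 18-month contrasts:

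- β + γ_18, the raw difference at 18 months;
- γ_18, the difference in change from baseline.

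Randomisation makes β zero in expectation, so both contrasts estimate the same quantity. Neither uses the knowledge that β is zero. The raw difference carries the chance baseline imbalance forward in proportion to the baseline to 18-month correlation. The change contrast subtracts all of it, which is too much whenever the regression slope of the 18-month score on baseline is below 1.

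At stake are precision that the collected data could supply, and a choice between two primary estimates that will differ by whatever imbalance occurs.

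**Working it through.** **Inputs.** From the Sample size calculation section: difference 0.5, SD 1.56 (REACT baseline data), 5% significance, 90% power, 206 per arm, 20% loss, 515 in total. Sidedness is not stated; two-sided reproduces the figure. The article gives no baseline to 18-month correlation r and no 18-month SD, so r is assumed from 0.3 to 0.7 and the SD is first held at 1.56 at every visit.

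**The plan's own figure.** Normal approximation: 2 × (1.960 + 1.282)² × 1.56² / 0.5² = 205 per arm. The noncentral t gives 206. Then 412 / 0.80 = 515. Power at 206 per arm is 90.2%. The stated numbers reproduce, and they are those of an unadjusted comparison of levels.

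**Variances with n per arm observed and equal SDs.**
- Raw difference: 2·SD²/n
- Difference in change: 4·SD²(1 − r)/n
- Baseline-adjusted: 2·SD²(1 − r²)/n

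Adjusted over raw is 1 − r²; adjusted over change is (1 + r)/2. Both are below 1 for any r strictly between 0 and 1.

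**Results at SD 1.56 and 206 per arm.** The raw SE is 1.56 × √(2/206) = 0.154.

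| r (assumed) | SE raw / change / adjusted | Power raw / change / adjusted | Variance saved against raw | Variance saved against change |
|---|---|---|---|---|
| 0.3 | 0.154 / 0.182 / 0.147 | 90.2 / 78.5 / 92.6% | 9% | 35% |
| 0.4 | 0.154 / 0.168 / 0.141 | 90.2 / 84.4 / 94.4% | 16% | 30% |
| 0.5 | 0.154 / 0.154 / 0.133 | 90.2 / 90.2 / 96.4% | 25% | 25% |
| 0.6 | 0.154 / 0.137 / 0.123 | 90.2 / 95.3 / 98.2% | 36% | 20% |
| 0.7 | 0.154 / 0.119 / 0.110 | 90.2 / 98.7 / 99.5% | 49% | 15% |

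**Incomplete follow-up.** A generalised least squares calculation for the three-visit model used 515 randomised, an assumed 10% missing at 6 months and 20% at 18 months, and equal correlations. It gives SEs of 0.1491 raw, 0.1491 change and 0.1323 with a common baseline mean at r = 0.5. The saving is 1 − (0.1323/0.1491)² = 21%. At r = 0.7 the SEs are 0.1452, 0.1163 and 0.1087. The loss shrinks a little but remains.

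**Gap between the two candidate estimates.** They differ by the fitted β. With 515 randomised 1:1, its SE is 1.56 × 2/√515 = 0.137, a 95% range of about ±0.27 points (1.96 × 0.137). That is over half the 0.5-point target, and this step needs no assumed correlation.

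**A wider 18-month SD.** Entry is restricted to SPPB 4 to 9 and later scores are not, so the 18-month SD may exceed 1.56. Take 2.0 as an assumption, with baseline SD 1.56 and r = 0.5. The change SD is √(1.56² + 2.0² − 2 × 0.5 × 1.56 × 2.0) = 1.82 and the adjusted SD is 2.0 × √0.75 = 1.73. Power is about 72% raw, 80% change and 83% adjusted.

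**The case against.** A repeated-measures model with baseline as an outcome and arm-by-visit terms is common and valid. Both contrasts are unbiased under randomisation, and the trial was sized for an unadjusted comparison: 206 per arm and 515 reproduce, and the raw difference keeps 90% power at SD 1.56. If the interaction coefficient is the intended estimate, baseline is at least subtracted. At r = 0.7 the power then lost is under one percentage point (98.7% against 99.5%). The change contrast falls below 90% only if r is under 0.5, and the article gives no r. The reference to change may also be general phrasing, since the same section powers a difference in level. All of this stands, and it makes the point one of efficiency rather than error.

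It does not remove the point. The article states the structure of the model, and under that structure both contrasts lose precision. An unseen analysis plan could constrain the baseline means, but that would alter the model described here.

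A reader might infer more than the article supports:

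- **Bias or inadequate planned power.** The reproduced figures and the unbiasedness of both contrasts rule this out on the plan's own inputs.
- **A constant-variance structure, or a joint test mixing 6 and 18 months.** The article specifies neither, and the abstract fixes the primary time point at 18 months.
- **Age and sex as part of the same fault.** The loose wording in the Adjusted analysis section is a minor, separate matter and says nothing about baseline SPPB.

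**Conclusion.** The concern holds as a free improvement to a valid analysis. As written, the primary model gives an 18-month effect that is either unadjusted for baseline or a difference in change. At equal variances and any correlation strictly between 0 and 1, both are less precise than the adjusted contrast.

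The direction of the loss is algebraic; its size depends on the assumed r. Against the raw difference the loss grows with r, and against change it shrinks with r, so whichever contrast is chosen there is a plausible range of r in which the loss is material. The possible gap between the two estimates rests only on the stated SD and sample size. It is the stronger reason to settle the wording before unblinding.

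**What to change.** Do one of the following in the protocol and the statistical analysis plan:

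- keep baseline SPPB in the outcome vector but drop the treatment term at baseline, so that the arms share a baseline mean (a constrained longitudinal model); or
- use baseline SPPB as a covariate, with 6 and 18 months as the outcome visits.

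In either case, name the treatment coefficient at 18 months as the single primary estimate and test. With a common baseline mean, the 18-month difference and the difference in change are the same parameter, so the ambiguity goes as well.

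The cost is wording only. No new data are needed because SPPB is measured on everyone for eligibility, and the sample size can stay as it is. The constrained model keeps every randomised participant; the covariate form keeps those with at least one follow-up score. Whether age and sex enter the primary model can be fixed in the same edit, as a minor separate item.
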